##### Paediatric Quality of Life Inventory–Multidimensional Fatigue Scale

The Paediatric Quality of Life Inventory–Multidimensional Fatigue Scale (PedsQL-Fatigue) is an 18-item questionnaire that measures overall fatigue, problems regarding sleep and/or rest, and cognitive fatigue [53]. This questionnaire is recommended for studies of children and adolescents after an ABI [25]. The feasibility, reliability and validity of the Dutch version of the PedsQL–Multidimensional Fatigue Scale are adequate, and the scale distinguishes healthy children from children with an impaired health condition [53].

##### Health Behaviour Inventory

The Health Behaviour Inventory (HBI) is a 50-item questionnaire. It measures (1) physical, (2) emotional, (3) cognitive and (4) behavioural symptoms. The HBI has sound psychometric properties and is able to distinguish MTBI from other injuries [25, 54]. Because a Dutch version of this inventory did not yet exist, we translated the original HBI into Dutch according to the translation guidelines [55].

##### Impact of Event Scale

The Dutch version of the Impact of Event Scale (IES-NL) is a 34-item questionnaire that measures possible post-traumatic stress responses [56]. The items are divided into four dimensions: (1) re-experiencing the stressor, (2) avoidance, (3) increased irritability and (4) child-specific responses. The IES-NL has adequate reliability across various traumatic stressors and reveals a robust structure over various samples [56]. Furthermore, the questionnaire is internationally recommended for studies of children and adolescents who have experienced an ABI [25].

##### Family Assessment Device–General Functioning Scale

The Family Assessment Device–General Functioning Scale (FAD-GF) is a 12-item questionnaire used to measure family functioning. It has been used in previous studies on brain injuries in children [31] and is recommended for studies of pre-injury family problems and changes in family functioning associated with the traumatic brain injury [25, 57, 58]. The psychometric properties of the FAD-GF are sufficient for assessing family functioning [59]. This questionnaire is used to evaluate pre-injury family functioning at T0 and post-injury family functioning at T2.

##### Child Behaviour Checklist

The Child Behaviour Checklist (CBCL) is a 113-item questionnaire widely used to measure behavioural and emotional problems and skills in children [60]. This questionnaire is recommended for examining these problems in children and adolescents who have experienced an ABI and has sound psychometric properties [25, 60]. It is used to assess pre-injury behaviour and emotional problems and skills at T0 and post-injury behavioural and emotional problems and skills at T2.

##### Sensory Profile–Dutch short version and Adolescent/Adult Sensory Profile–Dutch version

The Sensory Profile–Dutch short version (SP-NL) is a 38-item questionnaire. In this study, it is completed by the parents of patients between 6 and 11 years old. Patients aged 12 years and older complete the Adolescent/Adult Sensory Profile–Dutch version (AASP-NL). The questionnaires measure sensory information processing—including several sensory functions, movement abilities and social-emotional aspects—and assess the child’s activity and participation levels [61, 62]. The questionnaire adequately measures sensory information processing in children after a traumatic brain injury [63].

### Sample size

Sample size calculations for the cohort study are based on the available literature about MTBI prevalence and the expected number of participants who may visit the participating hospitals. Based on an inclusion period of 2 years, the aim is to recruit a sample of 500 children and adolescents who have experienced an MTBI. Assuming a 10 % dropout rate [64], our final sample should include 450 participants. Previous research shows that approximately 20 % of the population will experience long-term problems [13–16, 20–24, 30, 36] after an MTBI. Therefore, approximately 90 of our participants will experience long-term problems. When conducting the regression analysis to identify the predictors of the presence of long-term problems, we should include nine determinants, based on the assumption that approximately ten participants per determinant are needed for a reliable analysis [65].

Sample size calculations for the RCT are based on the results of studies on paediatric traumatic brain injury patients’ participation that relied on the parent-reports of the CASP-DLV. For the CASP-DLV, a standardized difference of 0.5 was expected [48]. With an α of 0.05 and a power of 0.8, a minimum of 63 children per group (control group and intervention group) is required for sufficient statistical power. Assuming a dropout rate of 10 %, the aim is to recruit at least 140 children and adolescents for the RCT.

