#### Cohort study

To determine the results of the primary outcome measure (CASP-DLV parent-reports), descriptive statistics will be used. Continuous variables will be expressed as the means and standard deviations or as medians with interquartile ranges, depending on the distribution values. Repeated-measures analysis of variance will be used to determine the difference in activities and participation over time. If a significant difference between the measurement points (*p* < 0.05) is found, a post hoc analysis based on Levene’s test will be performed.

Linear regression analysis will be used to identify the outcome predictors of activities and participation at 6 months post-injury, as measured by the CASP-DLV parent reports. Within 2 weeks after the injury, both continuous and categorical variables (i.e., injury and non-injury-related factors) are measured, as well as pre-injury family functioning (FAD-GF) and behaviour (CBCL); degree of fatigue (PedsQL-Fatigue); quality of life (PedsQL-QoL); sensory processing (SP/AASP-NL); physical, cognitive, emotional and behavioural post-concussive symptoms (HBI); post-traumatic stress (Schokverwerkingslijst [Impact of Event Scale–Dutch language version]); and participation in after-school activities (CAPE). Each variable will first be examined using univariate linear regression analysis to predict activities and participation. Next, variables with values of *p* < 0.2 in the univariate linear regression analysis will be included in the multivariate linear regression analysis. In the multivariate linear analysis, the significance level will be set at *p* < 0.05. For more clinically relevant purposes, outcome predictors will also be determined using logistic regression analyses. If the intervention is found to be effective (see statistical analyses of RCT study below), the data of the intervention group will be excluded from all of the cohort study analyses.

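### The cohort is sized for nine determinants of a binary outcome, but the analysis described is an uncapped p<0.2 screen of at least 22 candidates for a linear model, and the logistic model is not tied to the nine

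*Protocol article*

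**What the plan says.** **Protocol article, Sample size.** For the cohort, "the aim is to recruit a sample of 500 children and adolescents who have experienced an MTBI". After 10 % dropout, "our final sample should include 450 participants". The section takes it that "approximately 20 % of the population will experience long-term problems", so that "approximately 90 of our participants will experience long-term problems". It then turns to the model: "When conducting the regression analysis to identify the predictors of the presence of long-term problems", it says, "we should include nine determinants, based on the assumption that approximately ten participants per determinant are needed for a reliable analysis".

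**Protocol article, Statistical analyses, Cohort study.** The predictor analysis set out in detail is a linear regression of the CASP-DLV parent report at 6 months. The candidates are the injury-related and non-injury-related factors (Table 1) and a list of baseline questionnaires. "Each variable will first be examined using univariate linear regression analysis to predict activities and participation". Those reaching p<0.2 "in the univariate linear regression analysis will be included in the multivariate linear regression analysis", where 0.05 is the significance level. No maximum is set, and nine determinants are neither mentioned nor named. One further sentence adds logistic regression for clinical relevance. It gives no candidate list, selection rule or limit.

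The same section, like Outcome measurements, removes the intervention group's data from every cohort analysis if the intervention proves effective. The Sample size section makes no allowance for that loss.

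**The concern.** The sample-size argument and the analysis do not describe the same model. The route from 90 affected children to nine determinants is an events-per-variable rule, which belongs to a binary outcome. The analysis given in detail has a continuous outcome, a candidate list more than twice as long, and a data-driven entry rule that nothing ties to nine. The binary analysis, for which the count of nine was derived, is left without any rule.

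Identifying predictors is part of the study's first aim, and the Discussion promises insight into which children are at risk. The logistic model is the version the protocol offers for clinical purposes and the one most exposed to having too few events. Separately, choosing predictors by their univariate p-value affects what can be claimed from whichever model it is used in.

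**Working it through.** **1. The plan's own figures (Sample size section).**
- Final sample: 500 × (1 − 0.10) = 450
- Children with problems: 450 × 0.20 = 90
- Determinants: 90 / 10 = 9

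All three reproduce.

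**2. Number of candidates (Table 1 and Cohort study section).**
- Table 1: 7 injury-related + 9 non-injury-related = 16. Pre-injury CBCL and FAD-GF are among these, so they are not counted again.
- Further baseline measures in the Cohort study section: fatigue, quality of life, sensory processing, HBI, post-traumatic stress, CAPE = 6.
- Total: 16 + 6 = 22.

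This is a minimum if parameters are counted. Hospital has six sites and so takes five parameters: 22 − 1 + 5 = 26. Entering HBI or CAPE by domain would add more, but the plan does not say that it will.

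**3. Linear model (denominator: participants).**
- 450 / 22 = 20.5 per candidate; 450 / 26 = 17.3 per parameter
- Intervention arm excluded: 387 / 22 = 17.6 or 380 / 22 = 17.3

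Ten per determinant is met even if all 22 enter.

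**4. Logistic model (denominator: events), if the same candidates were used.**
- 90 / 22 = 4.1 per candidate; 90 / 26 = 3.5 per parameter
- Ten events for each of 22 candidates would need 220 events, so 220 / 0.20 = 1100 analysed and 1100 / 0.90 ≈ 1223 recruited.

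**5. Intervention arm excluded.** The RCT plans 140 children, so 70 per arm, or 63 after 10 % dropout. The 20 % rate is assumed to hold in those who remain.
- 450 − 63 = 387; × 0.20 = 77.4 events; / 10 = 7.7
- 450 − 70 = 380; × 0.20 = 76 events; / 10 = 7.6

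If ten is a floor, seven determinants are supported. Keeping nine would give 77.4 / 9 = 8.6 or 76 / 9 = 8.4 events each.

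**6. Does the p<0.2 screen itself keep the number to nine?** Assume 22 independent candidates.
- All null: 22 × 0.2 = 4.4 pass on average, and P(10 or more pass) = 0.006.
- If some true predictors always pass (an assumption), the chance that ten or more pass is:

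| True predictors | P(10 or more pass) |
|---|---|
| 5 | 0.24 |
| 6 | 0.40 |
| 7 | 0.60 |
| 8 | 0.80 |

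The screen may stay within nine, but it does not ensure it.

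**7. Effect of selection, whatever the sample size.** With 22 independent null candidates, about 22 × 0.05 = 1.1 reach p<0.05. Reported against all 22, that is the nominal 5 %. Reported within the 4.4 that survive the screen, it is 1.1 / 4.4 = 25 %. A null variable that has passed p<0.2 has a 0.05 / 0.2 chance of also being below 0.05, if its p-value changes little in the joint model.

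**8. Sensitivity to the event rate.** The Background gives 6 % to 43 % for symptoms at 6 months and beyond. Applied to 450, that is 27 to 193.5 events, or 1.2 to 8.8 per candidate for 22. Ten is not reached anywhere in that range. The range concerns symptoms, whereas the 20 % is the plan's figure for activity and participation problems, so it is only a rough bracket.

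**The case against.** A reader might infer that the planned analysis breaks the protocol's own ten-per-determinant standard. The documents do not support that, for three reasons.

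- The p<0.2 screen is written only for the linear model, where the denominator is participants and the standard is met with room to spare. The figure of 4.1 applies the linear model's candidate list to the binary outcome's events, and no section says the logistic model will use that list.
- The Sample size section does state nine for the regression on presence of problems. Which nine, and how they are chosen, may stand in a fuller protocol or analysis plan that is not shown.
- The stated ten is per determinant included, not per candidate screened. Under the null, the screen would very rarely admit ten or more.

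All three points stand, and they limit the finding. They do not remove it. The article does more than leave detail out: it fixes an outcome-driven entry rule, and that rule has the selection problem at any sample size. It also fixes an exclusion that would reduce the supported number below the nine it states. Counting candidates rather than survivors is a methodological position rather than the protocol's own rule. It is nonetheless the relevant count when selection uses the outcome, because the data have been used on every candidate tried.

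**Conclusion.** The point holds in limited form. The cohort size rests on 90 events and nine determinants for a binary outcome, while the analysis described is a linear regression with an uncapped screen of at least 22 candidates. For the linear model, ten per determinant is met (about 17 to 20 participants per candidate). For the logistic model it is not secured. It would be 4.1 events per candidate if the same list were used, and about seven determinants rather than nine are supported if the intervention arm is excluded. This is a missing safeguard, not a demonstrated breach.

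Apart from the counts, univariate selection can drop variables that matter only jointly with others. It also leaves the final p-values and confidence intervals too optimistic. That applies to the linear model as written, and to the logistic model if the screen is carried over.

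The figures assume 20 % with problems, 10 % dropout, one parameter per candidate unless stated, and, for the screening probabilities, independent candidates. The randomised comparison is not affected. The change should be made before the cohort data are analysed.

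**What to change.** - Remove the univariate p<0.2 step. Name the predictors in advance on clinical grounds, fit them together, and report the full model with all estimates and confidence intervals.
- Count parameters, not variables; hospital alone takes five.
- State in the Cohort study section that the logistic model is limited to nine parameters, and to seven if the intervention arm is excluded.
- The linear model may carry a larger pre-specified set, and the nine-parameter cap need not apply to it.
- If all 22 candidates are to be kept in the logistic model, penalised regression with optimism correction is an option.

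The cost is revised analysis wording and one team decision on the predictors, with no new data or recruitment. The downside is that fewer variables can be tested as predictors in the logistic model.

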### Statistical analyses

Descriptive statistics will be used to present the data on the participants, number of dropouts, losses during follow-up and the outcome measure scores. To determine the sample’s representativeness and the generalizability of the results, participants will be compared with non-participants based on the inclusion and exclusion criteria. Furthermore, the baseline characteristics of participants and dropouts, as well as patients lost during follow-up, will be compared. Comparisons will be performed using independent samples *t* tests or the non-parametric equivalent.

#### Cohort study

To determine the results of the primary outcome measure (CASP-DLV parent-reports), descriptive statistics will be used. Continuous variables will be expressed as the means and standard deviations or as medians with interquartile ranges, depending on the distribution values. Repeated-measures analysis of variance will be used to determine the difference in activities and participation over time. If a significant difference between the measurement points (*p* < 0.05) is found, a post hoc analysis based on Levene’s test will be performed.

Linear regression analysis will be used to identify the outcome predictors of activities and participation at 6 months post-injury, as measured by the CASP-DLV parent reports. Within 2 weeks after the injury, both continuous and categorical variables (i.e., injury and non-injury-related factors) are measured, as well as pre-injury family functioning (FAD-GF) and behaviour (CBCL); degree of fatigue (PedsQL-Fatigue); quality of life (PedsQL-QoL); sensory processing (SP/AASP-NL); physical, cognitive, emotional and behavioural post-concussive symptoms (HBI); post-traumatic stress (Schokverwerkingslijst [Impact of Event Scale–Dutch language version]); and participation in after-school activities (CAPE). Each variable will first be examined using univariate linear regression analysis to predict activities and participation. Next, variables with values of *p* < 0.2 in the univariate linear regression analysis will be included in the multivariate linear regression analysis. In the multivariate linear analysis, the significance level will be set at *p* < 0.05. For more clinically relevant purposes, outcome predictors will also be determined using logistic regression analyses. If the intervention is found to be effective (see statistical analyses of RCT study below), the data of the intervention group will be excluded from all of the cohort study analyses.

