Early recognition of symptoms and problems after an MTBI is crucial and enables the application of early and focused interventions [35, 36]. Long-term symptoms accompanying MTBIs, such as cognitive (e.g., attention) or behavioural symptoms, are often difficult to recognize or to associate with the MTBI [30]. Delayed recognition of these invisible symptoms, underestimation of these problems and delay of diagnosis frequently and unnecessarily lead to chronic and disruptive consequences, such as activity and participation limitations (e.g., in school and social relationships) [19, 37, 38]. Several studies indicate that early education, reassurance and even early cognitive behavioural approaches may be effective in preventing long-term problems after an ABI in both children and adults [39, 40], and, more specifically, after an MTBI [41–43].

Although the few available studies on interventions (e.g., psychoeducation) that prevent MTBI symptoms in children and adolescents have tended to report positive results, these studies have been retrospective or lacked a randomised controlled trial design [42–45]. The Brains Ahead! Study, using a randomised controlled trial and a large multicentre prospective cohort, is, to the authors’ knowledge, the first to examine the effect of a psychoeducational intervention on long-term activity and participation outcomes in children and adolescents who have experienced an MTBI.

The first aim of the Brains Ahead! study is to examine participation and activity levels in children and adolescents during the first 6 months after their MTBIs and to identify outcome predictors. We expect that 20 % of our study population will experience activity and participation problems during the first 6 months after their injuries [13–16, 20–24, 30, 36]. Furthermore, we hypothesize that injury-related and non-injury-related factors can predict outcomes [25–34].

The second aim is to investigate the effect of an early psychoeducational intervention on activities and participation. We hypothesize that, compared with usual care, our intervention will result in an increase in activities and participation during the first 6 months after an MTBI [39–45].

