## Methods/design

### Study design

The study is a multicentre prospective longitudinal cohort study with a nested single-blind randomised controlled trial (RCT). The RCT is conducted using a subset of participants from the cohort study (Fig. 1) [46]. The protocol is described according to the Standard Protocol Items: Recommendations for Interventional Trials (SPIRIT) checklist for clinical trials (see Additional file 1 for the SPIRIT checklist). Participants are followed during the first 6 months post-injury. During this period, there are three measurement points: 2 weeks (T0), 3 months (T1) and 6 months (T2) post-MTBI (Figs. 2 and 3). The intervention begins 2–4 weeks post-injury and ends 6 months post-injury. The measurements and measurement times are the same for the cohort study and RCT participants. Measurements are performed by the researcher, who is blinded to the RCT group assignment.

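### The cohort analysis names Levene's test as the basis of its post hoc step, so it cannot show between which of the three measurement points participation changed

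*Protocol article*

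**What the plan says.** The Study design section states that "there are three measurement points: 2 weeks (T0), 3 months (T1) and 6 months (T2) post-MTBI", so each child contributes up to three values of the same scale.

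Under Statistical analyses, Cohort study, the article takes the primary outcome in three steps:

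- Levels: "To determine the results of the primary outcome measure (CASP-DLV parent-reports), descriptive statistics will be used".
- Change over time: "Repeated-measures analysis of variance will be used to determine the difference in activities and participation over time".
- Follow-up: the trigger is worded "If a significant difference between the measurement points", at p < 0.05, and the action is that "a post hoc analysis based on Levene’s test will be performed".

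The subsection names no comparison of pairs of time points and no multiplicity adjustment for this step. Predictors are handled separately: "Linear regression analysis will be used to identify the outcome predictors of activities and participation at 6 months post-injury", with logistic regression in addition.

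**The concern.** A post hoc step after a significant time effect should locate the change: between 2 weeks and 3 months, between 3 and 6 months, or both. That is a question about means (or another measure of location) within the same children.

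Levene's test answers a different question. It asks whether the spread of scores differs between groups, and it assumes that the groups are independent. It therefore fails here on two counts: wrong parameter and wrong dependence structure.

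At stake is how the cohort reports the course of participation. With only two intervals between visits, whether recovery is complete by 3 months or continues to 6 months is the main thing a third measurement adds. An analyst who follows the sentence literally would reach this step because the means differ, and would then run a test that is almost blind to that difference.

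**Working it through.** **The plan's own figures.** No figure is attached to the post hoc step. The cohort size used below comes from the Sample size section: "the aim is to recruit a sample of 500 children and adolescents who have experienced an MTBI", less 10% dropout, gives 500 × 0.9 = 450, which matches the article.

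**What each procedure tests.** Write the three means as μ0, μ1, μ2 and the three standard deviations as σ0, σ1, σ2.

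| Step | Null hypothesis | Data structure assumed |
|---|---|---|
| Repeated-measures ANOVA | μ0 = μ1 = μ2 | same children at each point |
| Levene's test | σ0 = σ1 = σ2 | independent groups |
| Paired contrast, e.g. T1–T2 | μ1 = μ2 | same children at each point |

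The second row has no term for the means, so a rejection or non-rejection there carries no information on which means differ.

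**Illustration.** The article gives no CASP-DLV standard deviation, within-child correlation or time course, so these are assumptions: normal scores, equal variances, means 0, 0.3 and 0.5 SD, correlation r of 0.4, 0.6 and 0.8, n = 450, 2,000 simulated cohorts for each r. The contrasts are tested at 0.05/3 = 0.0167.

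| r | ANOVA rejects | Levene rejects | T0–T1 | T0–T2 | T1–T2 |
|---|---|---|---|---|---|
| 0.4 | 100% | 2.9% | 100% | 100% | 92.6% |
| 0.6 | 100% | 1.5% | 100% | 100% | 98.9% |
| 0.8 | 100% | 0% | 100% | 100% | 100% |

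Levene's test falls below its nominal 5% because positive correlation between the columns breaks its independence assumption. The shortfall grows with r.

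**Hand check of the weakest contrast (T1–T2, difference 0.2 SD, r = 0.4).** The SD of the paired difference is √(2(1 − r)) = √1.2 = 1.095. The expected t is 0.2/1.095 × √450 = 3.87. The two-sided critical value at 0.0167 with 449 degrees of freedom is 2.40. Power from the non-central t distribution is 92.9%, in line with the simulated 92.6%.

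**A smaller shift.** With means 0/0.2/0.3 SD and r = 0.6, the ANOVA rejects in 100% of runs and Levene's test in 1.3%. The paired contrasts reject in 98.9% (T0–T1), 100% (T0–T2) and 49.9% (T1–T2). The last figure is the ordinary power limit for a 0.1 SD difference.

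**The reverse case, with the ANOVA condition applied.** Suppose the means are identical and only the spread changes (assumed SDs 1, 0.85, 0.75). Run on its own, Levene's test rejects in 100% of runs. But the plan reaches the post hoc step only after a significant ANOVA, which happens in about 5 to 6% of runs here. A significant Levene result is therefore reached in only about 5 to 6% of cohorts.

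**The case against.** Three objections deserve a fair hearing.

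*The aim survives.* A reader might infer that the cohort's first aim cannot be answered at all. The article does not support that. The aim is "to examine participation and activity levels in children and adolescents during the first 6 months after their MTBIs and to identify outcome predictors". Levels come from the descriptive statistics, overall change from the ANOVA, and predictors from the regressions; none of these uses Levene's test. This objection stands in full, and the point is limited to locating the change.

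*Changes in spread would rarely be mistaken for changes in mean.* A reader might also infer that the plan would routinely declare a difference when only the spread moves. The ANOVA condition prevents this, as the last calculation shows. This objection also stands.

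*The wording may be looser than it looks.* The phrase can be read as saying that Levene's result guides the choice of a post hoc procedure. This does not rescue the sentence. No procedure is named for either result, and equality of variances between independent groups is not the relevant assumption check for a within-child factor with three levels.

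Two further inferences go too far. The article states no missing-data rule for the cohort, so it cannot be said to drop children who miss a visit; a condensed article may leave that to the full protocol or analysis plan. Nor is repeated-measures ANOVA itself an error because the RCT uses a multilevel model: it is a legitimate method for three time points.

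**Conclusion.** The point holds for the follow-up step only. The article does not merely leave the post hoc method open; it names one, and that method cannot do the job on either reading of the sentence. The cohort analysis can establish whether participation changed over 6 months but not between which measurement points.

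That conclusion rests on what Levene's test measures, not on the simulation. The percentages depend on the assumed mean shifts, equal variances, normal scores and correlation, and serve only as illustration. The RCT analysis and both sample sizes are untouched. Severity is moderate: the error is certain, but its reach is one secondary step of the cohort analysis.

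**What to change.** Replace the post hoc sentence in the Cohort study subsection with wording such as:

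> If the overall time effect is significant (p < 0.05), the paired contrasts T0–T1, T1–T2 and T0–T2 will be estimated with 95% confidence intervals and Bonferroni or Holm correction.

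Delete Levene's test from this step. The repeated-measures ANOVA can stay as it is.

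The cost is one sentence. No new data, visits or participants are needed.

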#### Primary outcome measure

The primary outcome measure, the Child and Adolescent Scale of Participation (CASP), is based on the activity and participation components of the International Classification of Functioning, Disability and Health for Children and Youth (ICF-CY). The CASP–Dutch language version (CASP-DLV) is a 20-item questionnaire designed specifically to measure activities and participation in children who have experienced an ABI [9]. It includes a parent-report and a self-report version for children aged 10 years and older. Our primary outcome will be limited to the results of the parent-reports. The CASP-DLV items are categorized into four domains: (1) participation at home, (2) participation in the district and residence, (3) participation at school, and (4) participation at home and in the environment. The questionnaire has been used in several international studies and has been recommended as an instrument for evaluating participation in children and adolescents after brain injury [34]. The internal consistency (Cronbach’s α 0.95) and test-retest reliability (intra-class correlation coefficient 0.90) of the CASP-DLV were found to be good and to have a significant correlation with the Paediatric Quality of Life Inventory (PedsQL) (concurrent validity 0.45) [48].

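### Cohort analysis: Levene's test is the wrong basis for the post hoc step after the repeated-measures ANOVA, because T0, T1 and T2 are the same children

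*Protocol article*

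**What the plan says.** Background gives the cohort's first aim as to "examine participation and activity levels in children and adolescents during the first 6 months after their MTBIs", together with identifying predictors. Under Study design, "there are three measurement points: 2 weeks (T0), 3 months (T1) and 6 months (T2) post-MTBI". Under Primary outcome measure, "Our primary outcome will be limited to the results of the parent-reports".

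The Cohort study subsection of Statistical analyses then sets out two steps:

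1. "Repeated-measures analysis of variance will be used to determine the difference in activities and participation over time".
2. "If a significant difference between the measurement points (*p* < 0.05) is found", then "a post hoc analysis based on Levene’s test will be performed".

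This subsection names no pairwise comparison of visits and no multiplicity adjustment for the second step. Levene's test appears nowhere else in the article, so nothing elsewhere corrects or explains the reference.

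**The concern.** The second step is conditional on a difference between measurement points, so its job is to show between which visits mean participation changed. Levene's null hypothesis is equality of variances across independent groups. It fits neither part of that job: it concerns spread, not level, and the design has one group of children seen three times.

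The sentence can be read in two ways.

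- **Levene's test is the post hoc analysis.** The result is then a statement about variances. It is also a global test over the three visits and points to no particular pair.
- **Levene's test selects the post hoc procedure.** This is the likelier meaning of a step described as based on the test. The procedures usually chosen this way are equal-variance or unequal-variance comparisons of between-subject groups, for example Tukey or Games-Howell (neither is named in the article). Applied to visits, they discard the within-child correlation that the ANOVA has just used. The variance condition that matters for repeated-measures ANOVA is sphericity, which Levene's test does not assess.

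At stake is whether the cohort can say correctly if participation changes mainly by 3 months or continues to change between 3 and 6 months.

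**Working it through.** The article gives no figure for this step, so there is none to reproduce. The check asks what each reading would do at the planned sample size.

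**Inputs**
- From the article (Sample size): "our final sample should include 450 participants", that is 500 × 0.9 = 450.
- From the article (Study design): three visits of the same children.
- Assumed, because the article gives no values: normal data; equal SDs, set to 1; a mean shift of 0.3 SD from T0 to T1 and a further 0.1 SD from T1 to T2 (0.4 SD in total); within-child correlation ρ = 0.4, 0.6 or 0.7.

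**Reading 1: Levene's test across the three visits.** In simulation (2,000 runs per setting) it rejects in about 2.6%, 1.0% and 0.4% of runs at ρ = 0.4, 0.6 and 0.7, although the means truly change. It does not respond to the change in level. Correlation between visits also pushes its rejection rate below the nominal 5%.

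**Reading 2: an independent-groups procedure, compared with within-child contrasts.** A normal approximation shows where the difference comes from.

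The true standard error of a difference between two visits is SE = √(2(1 − ρ)/450):
- ρ = 0.4: 0.0516
- ρ = 0.6: 0.0422
- ρ = 0.7: 0.0365

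*Paired contrast for T1–T2.* Power ≈ Φ(0.1/SE − z).
- Under Holm, the two larger contrasts are significant in practically every run, so T1–T2 is tested at 0.05 (z = 1.96). At ρ = 0.6: 0.1/0.0422 = 2.37, and Φ(0.41) = 0.66.
- Under Bonferroni (0.05/3, z = 2.394), at ρ = 0.6: Φ(−0.02) = 0.49.

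*Tukey on visits as independent groups.* The procedure uses SE = √(2/450) = 0.0667, whatever ρ is. With critical multiplier 2.346, the observed difference must exceed 2.346 × 0.0667 = 0.156 SD. Power ≈ Φ((0.1 − 0.156)/SE). At ρ = 0.6: Φ(−0.056/0.0422) = Φ(−1.34) = 0.09.

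| T1–T2 (0.1 SD), simulated power | ρ = 0.4 | ρ = 0.6 | ρ = 0.7 |
|---|---|---|---|
| Paired, Holm | 48% | 65% | 79% |
| Paired, Bonferroni | 32% | 49% | 64% |
| Independent-groups Tukey | 14% | 9% | 7% |

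The approximation gives 49/66/78%, 32/49/63% and 14/9/6%, in agreement.

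*The larger contrasts.* For T0–T1 (0.3 SD) at ρ = 0.4, the Tukey approximation gives Φ((0.3 − 0.156)/0.0516) = Φ(2.78) = 0.997, and more at higher ρ. The paired contrasts find T0–T1 and T0–T2 in practically all runs, and Tukey finds them in at least 99.6%.

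The independent-groups procedure therefore loses power for the small late change as correlation rises, while the paired contrast gains.

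**The case against.** The strongest reply has four parts.

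*The sentence does not say that Levene's test is the comparison of visits.* This stands. A reader might infer that the plan will test spread in place of level, but the wording fits procedure selection better. The article also names no pairwise procedure and no error term, so the Tukey figures show what usually follows from such a choice, not what the plan states. The objection does not rescue the sentence, because Levene's test has no valid role in choosing a procedure for repeated visits either.

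*A reader might infer a high risk of false claims of change when variances differ.* With equal means and SDs of 1.1, 1 and 1, a pairwise Levene test alone does reject in about 46% of runs. The plan, however, reaches the post hoc step only after a significant ANOVA, which with equal means occurs in about 5% of runs. Both reject in only about 2%. The document does not support a claim of frequent spurious change.

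*The power loss depends on the contrast and on the adjustment.* This stands in part. The loss concerns a small late shift, and the early change is found regardless. Against Bonferroni the gap is narrower, but it remains at every correlation tried. Against Holm, which also controls the familywise error, it is as large as in the unadjusted paired comparison.

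*An analysis plan may settle the post hoc method.* That would answer silence. Here a method is named, and it is unsuitable. A later plan must either inherit the error or depart from the published text.

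**Conclusion.** Wrong as written; should be fixed. Levene's test can neither locate a mean change across three visits of the same children nor validly select a procedure that does so.

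The size of the consequence depends on the reading and on assumed inputs. With 450 children, equal SDs and correlations of 0.4 to 0.7, an early shift of 0.3 SD is found either way if Levene's test only selects the procedure. A late shift of 0.1 SD would be found in 7–14% of runs by an independent-groups procedure, against 48–79% by Holm-adjusted within-child contrasts. If Levene's test were itself the post hoc test, it would reject in about 3% of runs or fewer and would still say nothing about means.

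A reader might infer that the study's main conclusions are at risk. The document does not support that. The overall test of time, the linear and logistic predictor regressions, the RCT's multilevel model and both sample sizes do not depend on this step. Only the cohort's statement of when participation changes is affected.

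**What to change.** Delete the reference to Levene's test and replace the clause with:

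*If the time effect is significant (Greenhouse-Geisser corrected, or from a mixed model with unstructured covariance), the within-child contrasts T1–T0, T2–T1 and T2–T0 will be estimated with 95% confidence intervals and Holm-adjusted p values.*

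The bracketed condition is needed because the overall test that gates the contrasts is valid only under sphericity, with a correction for its failure, or with a covariance model that does not require it.

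The cost is one sentence in the analysis section. It needs no new data, no change to visits or sample size, and can be made at any time before the cohort is analysed.
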